When pregnant women experience acute strokes, the systemic circulatory system may be severely affected, causing significant fluctuations in blood pressure that impact fetal blood flow [9]. These dramatic changes in fetal blood flow can lead to adverse intrauterine effects, such as fetal distress and neonatal asphyxia, potentially resulting in unfavorable outcomes for the offspring, thereby affecting the prognosis of the offspring [10]. However, no study has explored the impact of acute stroke in pregnancy and puerperium on the offspring and their future development. Besides, AMI (acute myocardial infarction) in pregnancy and ASPP may share a common pathophysiological mechanism, where their onset can be predisposed by physiological changes related to a hypercoagulable state, vascular endothelial remodeling, and alterations in insulin and lipid metabolism [11]. Only a few studies have explored the maternal and fetal outcomes of patients with AMI during pregnancy, and no study has assessed the future development of their offspring, mirroring the current research status of ASPP [12]. Therefore, it is important to understand the maternal and neonatal outcomes of these patients.

Establishing a cohort based on patients with ASPP is essential for addressing the aforementioned issues. Due to the rarity of ASPP, obtaining a sufficient sample size necessitates a nationwide, multicenter study. In 2020, the European Stroke Organisation proposed an international, multicenter, prospective cohort study to comprehensively explore ASPP patients [13]. However, no related study results have been reported to date. Moreover, the study protocol did not include the future development of the offspring of ASPP patients. The objectives of the ASPP study are as follows: (1) to explore the risk factors of ASPP and predictors of its prognosis; (2) to evaluate the risk of recurrent strokes, particularly during subsequent pregnancies, in ASPP patients; and (3) to assess the prognosis of offspring of ASPP patients.

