**Fig. 1 Fig1:**
[figure not shown]
The geographical distribution of centers participating in the ASPP study. The ASPP study aims to include 36 territorial or regional centers across 22 provinces in China

ASPP patients and non-ASPP participants from January 2015 to November 2024 will be included (Fig. 2). Table 1 lists the inclusion criteria and exclusion criteria. ASPP patients are defined as those who experience acute stroke events during pregnancy or within 6 weeks postpartum, confirmed by neuroimaging evidence of cerebral infarction or hemorrhage corresponding to their symptoms.

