**Fig. 2 Fig2:**
[figure not shown]
Study design flowchart of the ASPP cohort

**Table 1 Tab1:** Inclusion and exclusion criteria

**Inclusion criteria** (1) Aged ≥ 18 years (2) Who are pregnant or within 6 weeks postpartum (3) Patients, their legally acceptable representatives, or relatives who agree to collect personal information for this study and sign an online written informed consent **Exclusion criteria** (1) Missing critical baseline demographic, clinical, or neuroimaging data The key data includes the following: • Age • Body mass index (BMI) • Preexisting conditions (such as a history of hypertension, diabetes, and other chronic diseases) • History of previous strokes • Neuroimaging results (such as CT or MRI findings) (2) Whose offspring have congenital malformations or inborn errors of metabolism (3) With complications affecting cerebral blood flow, such as amniotic fluid embolism during pregnancy (4) The patients’ family members (excluding parents and siblings) have a history of severe mental illness, such as intellectual disability and schizophrenia. In addition, autism spectrum disorder (ASD) is considered a neurodevelopmental disorder, distinct from the traditional definition of mental illness; therefore, it is not included in the exclusion criteria for a family history of severe mental illness (5) Who undergo AMI during pregnancy (6) Who experience non-spontaneous stroke events due to other causes, such as cerebral infarction or hemorrhage caused by surgery	

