### Data collection and management

Baseline data collection will be conducted through the electronic medical record (EMR) system of the participating centers. If certain variables are not recorded in the EMR, they will be collected retrospectively through telephone interviews. Table 2 presents the variables to be collected at baseline. A specialized secure database (CRF, case report form) will be established to facilitate the collection of standardized data from different centers. All data will be anonymized to ensure privacy, and each patient included in this study will be identified by an identity number. General variables (such as demographics, medical history, and medication history) and pregnancy- or puerperium-associated variables (including data on delivery and offspring-related variables) will also be collected for non-ASPP participants.

**Table 2 Tab2:** Baseline variables

• **Demographics**
▪ Age
▪ Ethnic: Han or other
• **General clinical variables**
▪ Date of admission and discharge
▪ BMI (calculated based on prepregnancy weight and height data)
▪ Previous or current smoking
▪ Previous or current drinking
▪ Previous or current drug abuse
▪ NIHSS and/or mRS at admission and discharge
▪ Blood routine index: RBC, WBC, PLT, etc.
▪ Blood biochemical index: TC, HDL-C, etc.
▪ Coagulation function index: TT, PT, FIB, APTT, etc.
▪ Other blood index: lupus anticoagulant, anticardiolipin antibodies, etc.
• **Medical history**
▪ Hypertension (if with record maximal SBP and DBP)
▪ Diabetes
▪ Migraine
▪ Polycystic kidney disease
▪ Cerebral vascular disease (if with record etiology)
▪ Myocardial infarction or angina
▪ Congestive heart failure
▪ Known atrial fibrillation or flutter
▪ Valvular heart disease
▪ Hypercholesterolemia
▪ Pulmonary embolism

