#### Primary outcome

These are the following: For Aim 1, composite unfavorable outcome defined as *mRS* > 2 or EQ-5D index score < 0.7 at follow-up; for Aim 2, recurrent strokes confirmed by neuroimaging; and for Aim 3, the Apgar scores of newborns and results from Ages & Stages Questionnaires, Third Edition (ASQ-3) at follow-up.

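### Exclusion criterion 4 is incoherent as printed: an affected aunt or cousin removes a woman but an affected mother or brother does not, and her own child's intellectual disability could count

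*Protocol article*

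**What the plan says.** Table 1, exclusion criterion 4, removes women whose "family members (excluding parents and siblings) have a history of severe mental illness, such as intellectual disability and schizophrenia". The same entry then deals with autism spectrum disorder, explaining that it is neurodevelopmental and that "it is not included in the exclusion criteria for a family history of severe mental illness". So the article regards the rule as a family-history exclusion. It gives a reason for the autism exception and none for the parent and sibling exception.

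The third objective in the Background is "to assess the prognosis of offspring of ASPP patients". Under Primary outcome, Aim 3 includes "results from Ages & Stages Questionnaires, Third Edition (ASQ-3) at follow-up". Table 1 does not tie criterion 4 to this or any other aim.

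On data, the article says that "Table 2 presents the variables to be collected at baseline". Family psychiatric history is not among the items in that table, and the Statistical analysis section does not name it as an adjustment variable. Under Data collection and management, variables not recorded in the medical record are collected retrospectively by telephone.

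**The concern.** An exclusion for family history normally works by closeness: the nearer the affected relative, the stronger the reason to exclude. This one exempts two classes of near relative and leaves an undefined remainder to trigger exclusion. If it is meant to keep familial developmental risk out of the ASQ-3 comparison, it does not do so consistently.

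Three things are at stake.

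- Centers may apply it differently. There are 36 planned centers, and family members is not defined.
- The remainder includes the woman's own children. If the study child counts, eligibility depends on the outcome.
- Women with a rare condition are removed from Aims 1 and 2 (functional outcome and recurrent stroke), where the criterion has no evident role. The Sample size estimates section puts the recurrence requirement at 456 cases against a target of 400, already 456 − 400 = 56 short.

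**Working it through.** The plan gives no figure to reproduce. The check is to apply the printed rule to each kind of relative and see whether any ordering fits.

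| Affected relative of the woman | Degree to the woman | Degree to the study child | Literal result |
|---|---|---|---|
| Parent | first | second (grandparent) | stays in |
| Sibling | first | second (aunt or uncle) | stays in |
| Another child of hers | first | first if full sibling | excluded |
| Spouse, if counted as family | not a blood relative | first, if the child's father | excluded |
| Grandparent | second | third | excluded |
| Aunt or uncle | second | third | excluded |
| Cousin | third | fourth | excluded |

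**Ordered by closeness to the woman.** Parents and siblings (first degree) are kept, while second- and third-degree relatives exclude. That is inverted, and her own children, also first degree, exclude.

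**Ordered by closeness to the child.** First-degree relatives exclude, second-degree maternal relatives do not, and third- and fourth-degree relatives do. That is not an ordering either.

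**The one coherent reading.** If family members means only spouse, children, parents and siblings, removing the last two leaves spouse and children, and the rule excludes on the child's nearest relatives other than the mother. Nothing in Table 1 limits the term in this way.

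**If *excluding* should read *including*.** The inversion disappears, but the rule then reaches every relative without limit, and the study child is still not set aside.

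**The study child.** Participants date from January 2015 to November 2024, and the first follow-up is December 2024 to February 2025. A child born in 2020 is about four at that follow-up, so a diagnosis may already be known when eligibility is judged. If that diagnosis excluded the mother, children with the worst development would leave the ASQ-3 comparison. Should ASPP impair development, more would leave the ASPP group and the contrast would shrink.

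**Size.** The document gives no prevalence of family mental illness and no count of women removed. For illustration only, assume that 3% of women have an affected parent or sibling and that their children's risk of a below-threshold result is 20% rather than 10%. Keeping these women adds 0.03 × (0.20 − 0.10) = 0.003, or 0.3 percentage points, to a group's rate. The effect on the contrast is (p₁ − p₀) × 0.10, where p₁ and p₀ are the shares in the two groups. It is 0 when both are 3%, and 0.3 points in the extreme case of 3% in one group and none in the other. The loss of women through other relatives cannot be estimated.

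**The case against.** The strongest objection concerns the reference person. ASQ-3 is measured on the child, and the woman's parents and siblings are the child's second-degree relatives. The relatives who still trigger exclusion can include the child's father and siblings, who are closer. A reader might infer that the rule keeps the closest family history and drops only remote ones. The document does not support that for the ASQ-3 outcome. This part of the objection stands, but it does not rescue the rule, because more distant relatives trigger exclusion as well.

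Second, the purpose is nowhere stated, and no passage shows that family psychiatric history is associated with ASPP. A reader might infer that a known confounder is left uncontrolled. That too goes beyond the text: bias needs prevalence or recall to differ between the groups.

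Third, the parenthesis may be a wording slip rather than a choice. The document cannot settle this. A slip would still leave a printed criterion different from the one meant.

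Fourth, the article provides for telephone collection and acknowledges recall and information bias in its limitations. Both are true. That psychiatric history in the extended family is often missing from hospital records is a judgement, not something the article states. The absence of the variable from Table 2 also does not prove that the full case report form lacks it.

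**Conclusion.** The point holds as a defect in a stated eligibility rule. As printed, criterion 4 fits no kinship ordering without a restriction that the text does not contain, its exemption is unexplained, and it can be read to exclude on the study child's own development. It also applies to aims for which it has no evident purpose.

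The conclusion rests on the plain reading of the parenthesis and of family members. The link to Aim 3 is an inference from the outcomes. The 0 to 0.3 point range depends entirely on assumed inputs, so it does not show material bias in the ASQ-3 result. Any effect is probably small. The reason to act is that the wrong women may be removed, in ways that can vary by center, and that the correction is cheap.

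**What to change.** Rewrite criterion 4 to name the relatives meant by kinship to the child, for example the mother, the father, and the mother's parents and siblings. State that the study offspring do not count, say whether the child's older siblings do, drop more distant relatives and give the reason for the rule. Apply it identically to the groups compared and only to the Aim 3 ASQ-3 analysis, so that ASPP cases are not lost from Aims 1 and 2.

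Alternatively, remove the exclusion, record the same family history for everyone in Aim 3, and enter it as a covariate in the ASQ-3 model. This loses no participants.

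If centers have already applied the criterion, count the women removed under it by group and reassess them against the corrected text.

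The cost is one rewritten entry in Table 1 and one CRF item. That item will still depend partly on recall.

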Grouping of non-ASPP participants is as follows:Non-ASPP participants include two matched control groups: The first group consists of participants in the pregnancy or postpartum period without a history of stroke (pregnancy/postpartum non-stroke group); the second group consists of nonpregnant or non-postpartum participants who have recently experienced a stroke (nonpregnant stroke group).Matching criteriaFor the pregnancy/postpartum non-stroke group, controls will be matched to ASPP cases in a 1:1 ratio based on age (±2 years) and hypertension history, with the latter stratified into preexisting hypertension, pregnancy-induced hypertension, or no hypertension.For the nonpregnant stroke group, a 1:1 matching strategy will be applied using age (±2 years), stroke etiology (classified by TOAST criteria), and preexisting hypertension status.Classification of pregnancy-related etiologies is as follows:Postpartum vascular diseasePregnancy-related hypercoagulable statesPregnancy-induced hypertensionPreeclampsiaAmniotic fluid embolismMatching of nonpregnant/postpartum patientsAge matching (±2 years)Matching based on stroke etiology, such as cardiogenic stroke, atherosclerotic stroke, small vessel disease stroke, and other identifiable causes (e.g., intracerebral hemorrhage)Health status and comorbidities, including common comorbidities such as cardiovascular disease, hypertension, and diabetesLifestyle factors, such as smoking and alcohol consumption historyDiscussion of the impact of pregnancy-related etiologiesEtiological characteristics, such as thrombosis resulting from pregnancy-related hypercoagulable states, hemodynamic changes caused by postpartum vascular disease, and hypertensive lesions associated with preeclampsiaPhysiological changes: Physiological changes during pregnancy, such as increased blood volume, blood pressure fluctuations, and alterations in coagulation mechanismsPsychological and social factors: Assessing the unique challenges faced by pregnant women in coping with stress, anxiety, and other mental health issues, as well as their potential impact on stroke occurrenceImpact assessment: When comparing ASPP patients with nonpregnant stroke patients, the influence of pregnancy-related etiologies on stroke recurrence rates and long-term prognosis will be clearly delineated.

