▪ Neurologic: Intracerebral rebleeding (hemorrhagic stroke), vasospasm or delayed cerebral ischemia, intracerebral hemorrhage (ischemic stroke), brain herniation, etc.
▪ Systemic: Chest infection, urinary tract infection, deep venous thrombosis, pulmonary embolism, gastrointestinal bleeding, myocardial ischemia, etc.
• **Offspring-related variables**
▪ Term at birth: Pre-term, full-term, or post-term
▪ Gender
▪ Birth date
▪ Birth weight
▪ Apgar scores at 1, 5, and 10 min
▪ Transfer to NICU (if with record etiology)

*BMI* body-mass index, *NIHSS* National Institute of Health stroke scale, *mRS* modified Rankin Scale, *RBC* red blood cell, *WBC* white blood cell, *PLT* platelet, *TC* total cholesterol, *HDL-C* high-density lipoprotein cholesterol, *TT* thrombin time, *PT* prothrombin time, *FIB* fibrinogen, *APTT* activated partial thromboplastin time, *SBP* systolic blood pressure, *DBP* diastolic blood pressure, *AVM* arteriovenous malformation, *IA* intracerebral aneurysm, *CT* computed tomography, *CTA* computed tomography angiography, *MRI* magnetic resonance imaging, *MRA* magnetic resonance angiography, *DSA* digital subtraction angiography, *ECG* electrocardiography, *NICU* neonatal intensive care unit

^a^The first trimester is defined as the period from conception to 12 + 0 weeks of gestation. The second trimester spans from 12 + 1 weeks to 28 + 0 weeks of gestation. The third trimester begins after 28 + 1 weeks of gestation. Puerperium is defined as the period within 6 weeks postpartum

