### Study outcomes

This study will focus exclusively on the short-term follow-up outcomes for women and their offspring. Specifically, short-term outcomes are defined as events occurring during hospitalization, with particular attention to the following aspects:Complications: Assessment of complications related to postpartum stroke, including the risk of stroke recurrence, cardiovascular complications (such as heart failure and arrhythmias), and infection risks (such as pulmonary or urinary tract infections)Medical interventions: Documentation of treatments administered during hospitalization, including antiplatelet or anticoagulant therapies, antihypertensive medication, antibiotic use, and physical therapy interventions, to evaluate their effectiveness and patient responseChanges in health status: Close monitoring of overall health fluctuations during the hospital stay, including neurological function, blood pressure control, heart rate stability, and emotional state, to comprehensively assess health variations throughout treatment

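### Exclusion criterion 5 (AMI in pregnancy) has no time limit relative to the index stroke, so ASPP cases can be removed for a post-stroke event, with no stated equivalent for the nonpregnant stroke controls

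*Protocol article*

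**What the plan says.** Exclusion criterion 5 in Table 1 consists of the words "Who undergo AMI during pregnancy". It does not place the infarction before or after the stroke, and it does not name the puerperium. The ASPP definition just before the table covers pregnancy and the 6 weeks after delivery.

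Elsewhere the article treats cardiac events as data to be collected:

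- Table 2, systemic complications, ends with "gastrointestinal bleeding, myocardial ischemia, etc".
- Study outcomes names "cardiovascular complications (such as heart failure and arrhythmias") among the short-term complications to be assessed.
- Table 2, medical history, records "Myocardial infarction or angina" as a baseline variable. Data collection and management says that medical history is also collected for non-ASPP participants.
- Background says that AMI "in pregnancy and ASPP may share a common pathophysiological mechanism".

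The text introduces the table with "Table 1 lists the inclusion criteria and exclusion criteria", directly after naming both ASPP and non-ASPP participants. Inclusion criterion 2, however, reads "Who are pregnant or within 6 weeks postpartum", which a nonpregnant stroke control cannot meet. The paragraph on grouping and matching then says that ASPP and nonpregnant stroke patients will be compared on recurrence and long-term prognosis.

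**The concern.** The study is retrospective. When a site screens a chart, everything that happened after the stroke is already in the record. A criterion without a time anchor is then applied to post-stroke events as readily as to pre-stroke ones, and eligibility comes to depend on part of the clinical course under study.

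Three things follow from the wording. The most severe form of a complication that Table 2 collects becomes a reason for removal if it occurs before delivery. The same event after delivery is kept, although both periods belong to the exposure window. And the rule cannot by its terms operate in the nonpregnant stroke group, so in that comparison only one side is selected on it.

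At stake are the comparison of recurrence and long-term prognosis between the two stroke groups, and the count of myocardial complications after antepartum stroke.

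**Working it through.** The article gives no figure on this point, so there is none to reproduce. The check is a reading of the criterion case by case, followed by a sensitivity calculation.

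**Criterion 5 as worded, applied to an AMI in the index pregnancy or its puerperium**

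| Situation | Effect |
|---|---|
| Antepartum stroke, AMI earlier in the same pregnancy | Excluded, on a pre-index event |
| Antepartum stroke, AMI later but before delivery | Excluded, on a post-index event |
| Antepartum stroke, AMI in the puerperium | Kept |
| Postpartum stroke, AMI in the pregnancy | Excluded, on a pre-index event |
| Postpartum stroke, AMI in the puerperium | Kept |
| MI before the pregnancy | Kept, recorded as medical history |
| Nonpregnant stroke control, AMI before or after stroke | No rule stated in the article |

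The second row is the defect. The third and fifth rows show that the puerperium is treated differently, with no reason given. The last row shows the asymmetry.

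**Sensitivity calculation for recurrence**

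Inputs:

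- f, the fraction of otherwise eligible ASPP cases removed by criterion 5. The documents do not give it; 0.25% to 5% is assumed. Counts are per 400 women, the target in Sample size estimates.
- R, the recurrence risk of removed women relative to the rest. The documents do not give it; 1.5 to 5 is assumed.

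Let p be the risk in the women who stay. The risk without the exclusion is (1 − f)p + fRp = p[1 + f(R − 1)]. With the exclusion it is p. If the control risk is unchanged, the ASPP-to-control risk ratio is multiplied by

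1 / [1 + f(R − 1)].

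Example: f = 1%, R = 5 gives 1 / (1 + 0.01 × 4) = 1 / 1.04 = 0.962.

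| f | Women per 400 | R = 1.5 | R = 5 |
|---|---|---|---|
| 0.25% | 1 | 0.999 | 0.990 |
| 1% | 4 | 0.995 | 0.962 |
| 2% | 8 | 0.990 | 0.926 |
| 5% | 20 | 0.976 | 0.833 |

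For f up to 1% the reduction is below 4%. It reaches about 17% only when 5% of cases are removed and they carry 5 times the risk. For each f and R these are upper bounds, for two reasons. The formula allows no offset from matching. And f counts every AMI in pregnancy, including those before the stroke, which an exclusion limited to pre-index events would still remove.

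**The case against.** The strongest reply is that the criterion is meant to remove a separate disease. Background presents AMI in pregnancy as a parallel condition, and Table 2 collects myocardial ischemia as a complication, so post-stroke cardiac events are evidently meant to be counted. The complications named as examples in Study outcomes, heart failure and arrhythmias, are not touched by criterion 5. That may well be the intention, but the criterion does not say so, and a site that applies it literally will exclude.

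The second reply concerns the controls. Inclusion criterion 2 shows that Table 1 cannot be the full eligibility list for nonpregnant women. Their criteria may stand in Fig. 2 or in the full protocol, neither of which is shown. This stands: the missing control rule is a matter to confirm, not a proven gap. It does not answer the timing defect, which lies in the stated criterion.

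A reader might infer that the nonpregnant group keeps all the high-risk cardiac patients that the ASPP group loses. The documents do not support that. Earlier infarction is recorded at baseline and excludes nobody in either group. Controls are matched 1:1 on stroke etiology, and the second matching list adds cardiovascular disease, so they partly follow the cardiac profile of the cases that remain. The first matching list has no cardiac history, so the extent of this offset is unclear. Matching on baseline features cannot balance an AMI after the stroke.

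A reader might also try to express the bias as in-hospital mortality, taking the 4.2% quoted in Background as the rate in women without AMI. The article gives that figure for pregnant women with acute stroke and states no AMI exclusion, so it cannot serve as an AMI-free rate. Nor does the article give the frequency or mortality of AMI among cases. No mortality figure is claimed here.

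**Conclusion.** The point holds in a limited form. As worded, criterion 5 can remove antepartum-stroke cases because of an event after the index stroke. It treats the two parts of the exposure window differently, and it has no stated counterpart in the nonpregnant stroke group. In the comparison with that group, the direction is towards a lower apparent ASPP risk, provided that women with AMI have the worse prognosis.

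The size cannot be obtained from the documents and is probably small: under 4% on the recurrence risk ratio with f up to 1% and R up to 5, both assumed. The post-index problem itself concerns antepartum strokes only, since an AMI in the index pregnancy always precedes a postpartum stroke. The comparison with pregnant or postpartum women without stroke is not made asymmetric in this way, because they fall under the same exclusion.

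This is an eligibility wording fault that is worth correcting because the correction is simple. It does not undermine the study.

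**What to change.** - Limit criterion 5 to AMI that occurred before the index stroke.
- Word it alike for pregnancy and the 6 puerperal weeks.
- Apply the same pre-index rule to the nonpregnant stroke controls over an equal look-back period, or confirm that their own criteria already do so.
- Count an AMI after stroke onset as a complication in both stroke groups.
- Reconcile the two matching lists for the nonpregnant stroke group, so that it is clear whether cardiovascular disease is a matching factor.

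The change to the text is about one line in Table 1, but some rework follows. The enrolment window ended in November 2024 and the first follow-up round was scheduled for December 2024 to February 2025. The few records screened out under criterion 5 must be rechecked, and a few women may be added or removed. Anyone added would need consent and may have missed the first round.

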**Design:**

This study is a retrospective, observational, nationwide, multicenter research project planned to include 400 ASPP patients from 36 centers across 22 provinces in China, from 2015 to 2024. ASPP is defined as acute ischemic or hemorrhagic stroke during pregnancy or within 6 weeks postpartum, confirmed by neuroimaging. Two matched groups will be included for comparison: 400 pregnant/puerperal participants without a stroke history and 400 nonpregnant/puerperal participants with a recent stroke, matched by age and/or stroke etiology.

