**• Medication history**
▪ Antihypertensive (if with record the duration of antihypertensive medication use, including pre-pregnancy and during pregnancy, and the types of medications, such as methyldopa, labetalol, amlodipine)
▪ Antiplatelet
▪ Oral contraceptive
• **Stroke evaluation**
▪ Type: Ischemic (thrombotic, embolic) or hemorrhagic (intracerebral, subarachnoid)
▪ Etiology
(1) Ischemic stroke (carotid stenosis, intracranial atherosclerotic stenosis, cardiogenic embolic stroke, arterial dissection, pregnancy-related hypercoagulable state, moyamoya disease)
(2) Hemorrhagic stroke (AVM, IA, pregnancy-related hypercoagulable state)
(3) Other stroke types: Cerebral venous thrombosis, cerebral sinus thrombosis, stroke caused by systemic inflammation, hematological disorders (such as thalassemia, aplastic anemia), arterial dissection (such as carotid dissection), cardiovascular diseases (such as valvular heart disease, embolism due to atrial fibrillation)
▪ Location and size: Anterior or posterior circulation, cortical or subcortical
▪ Diagnostic neuroimaging: CT, CTA, MRI, MRA, DSA, etc.
▪ Cardiac examination: ECG, echocardiography, etc.
• **Pregnancy-/puerperium-associated variables**
▪ Week of gestation and trimester at stroke onset^a^
▪ Gestational hypertension
▪ Preeclampsia/eclampsia
▪ HELLP syndrome
▪ Gestational diabetes
▪ Frequency of previous pregnancy and pregnancy-/puerperium-associated stroke
• **Data on delivery**
▪ Type: Spontaneous vaginal delivery, cesarean section, or prenatal termination (induced abortion or labor)
▪ Week of gestation at delivery
• **Stroke management**
▪ Ischemic stroke
(1) Nonsurgical treatment (if with record dose and duration): anticoagulant (heparin, warfarin), antiplatelet (aspirin, clopidogrel), intravenous thrombolysis (alteplase, tenecteplase), etc.
(2) Surgical treatment: mechanical thrombectomy, etc.
▪ Hemorrhagic stroke
(1) Nonsurgical treatment: Supportive (blood pressure control, intracerebral pressure control), etc.
(2) Surgical treatment: Open surgery (clipping for IA, excision for AVM, hematoma evacuation), endovascular intervention (coiling for IA, embolization for AVM), ventriculopuncture drainage, etc.
▪ Time relationship with terminating the pregnancy (if with surgical treatment): after, before, or during the same period
• **Complications**

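### In the Aim 1 risk-factor comparison, pregnant/puerperal controls may have no prior stroke but cases may, so no valid odds ratio for prior stroke can come from it

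*Protocol article*

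**What the plan says.** The Design section makes the first part of the study a case-control study of risk factors for ASPP.

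- **Controls.** Under Participating centers and patient population: "The first group consists of participants in the pregnancy or postpartum period without a history of stroke". The Abstract (Design) agrees: "400 pregnant/puerperal participants without a stroke history".
- **Cases.** In the same Methods section: "ASPP patients are defined as those who experience acute stroke events during pregnancy or within 6 weeks postpartum", confirmed by imaging. Nothing limits this to a first stroke.
- **Table 1.** None of the six exclusions removes a woman because of an earlier stroke. The item "History of previous strokes" appears only in the list of key data that must not be missing.
- **Table 2.** Baseline data include a history of cerebrovascular disease and "Frequency of previous pregnancy and pregnancy-/puerperium-associated stroke". Data collection and management says that medical and medication history are also collected in non-ASPP participants.
- **Matching and analysis.** The first control group is matched 1:1 on age (±2 years) and hypertension history. Statistical analysis plans multivariate logistic regression for independent predictors, with significance at p < 0.05.

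**The concern.** In a case-control study, a control should be a woman who would have been counted as a case had she had the outcome. Here a woman with an earlier stroke and an uneventful pregnancy cannot be a control. The same woman would be a case under the stated definition if she had a stroke in that pregnancy. The two groups thus have different eligibility on a variable that the study records and that an analyst looking for risk factors would naturally examine.

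At stake is any Aim 1 estimate for prior stroke from this comparison, because the zero among controls comes from selection and says nothing about how common prior stroke is in pregnant women without a new stroke. To a lesser degree, estimates for factors that accompany prior stroke are also at stake.

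**Working it through.** The plan states no figure on this point, so there is none to reproduce.

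**Inputs.** 400 cases and 400 matched controls (Abstract, Design); threshold p < 0.05 (Statistical analysis), taken as two-sided, which is an assumption. The prevalence of prior stroke is not in the article, among cases or among pregnant women generally. All prevalences below are assumptions.

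**1. Odds ratio.** With *a* cases with prior stroke and 0 controls:

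- Unmatched: OR = (a × 400) / ((400 − a) × 0), infinite for any a ≥ 1.
- Matched pairs: OR = b/c, where c counts pairs in which only the control has had a stroke. By design c = 0 and b = a.

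In a logistic model this is separation: the likelihood keeps rising as the coefficient grows. Penalised (Firth) estimation would return a finite number, but not a valid one, because the empty cell was made by the selection rule.

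**2. How few cases reach significance.** Exact McNemar p = 2 × 0.5^b:

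| Cases with prior stroke | Exact McNemar p | Fisher p (a/400 v 0/400) |
|---|---|---|
| 5 | 2 × 0.5^5 = 0.063 | 0.062 |
| 6 (1.5%) | 2 × 0.5^6 = 0.031 | 0.031 |

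**3. How likely each result is.** With prevalence *p* among 400 cases, P(at least one) = 1 − (1 − p)^400, and P(six or more) is the binomial tail:

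| Assumed p among cases | Expected cases | P(infinite OR) | P(significant) |
|---|---|---|---|
| 0.2% | 0.8 | 55% | about 0 |
| 0.5% | 2 | 87% | 1.6% |
| 1% | 4 | 98% | 21% |
| 1.5% | 6 | 99.8% | 56% |
| 2% | 8 | about 100% | 81% |
| 3% | 12 | about 100% | 98% |

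The last column is a false-positive rate only if the true odds ratio is 1, that is, if pregnant women generally have the same prevalence *p*. With equal eligibility and a true odds ratio of 1, simulated exact McNemar tests gave false-positive rates from 1.9% (p = 1%) to 3.3% (p = 5%).

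**4. Spill-over to other factors.** Let π be the prevalence of prior stroke among potential controls, and let a factor have frequency f in those with prior stroke and g in those without. Controls show g under the rule and (1 − π)g + πf without it. The difference, π(f − g), cannot exceed π. At π = 0.2% that is at most 0.8 of 400 controls; at 0.5%, 2 of 400; at 1%, 4 of 400. The shift is small in absolute terms. It weighs most on a rare factor carried mainly by women with prior stroke, such as cerebrovascular disease history.

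**The case against.** **Case eligibility is read from silence.** No sentence says that women with prior stroke are enrolled as cases, the flowchart is not shown, and recording stroke history is needed anyway to verify control eligibility. This stands as a limit on certainty. Yet the case definition and the exclusion list are both given, and neither restricts cases. The count of earlier pregnancy-associated strokes must also be zero in every pregnant control, so within this comparison it can vary only among cases.

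**No text names prior stroke as a risk factor to be tested.** Table 2 serves all three aims, and the logistic model's covariates are not listed. Separation therefore arises only if the term is entered. This stands, but nothing in the article keeps the term out.

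**Stronger readings that the document does not support.** A reader might infer:

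- *That a spurious significant effect is to be expected.* Six or more prior strokes among 400 cases with a true odds ratio of 1 would mean roughly 1.5% or more of ordinary pregnant women having had a stroke. The article gives no such prevalence. At an assumed 0.2%, zero among 400 controls would occur 45% of the time with no rule at all (0.998^400 = 0.449). If the population rate is well below that in cases, the direction of the association is right and only its size cannot be estimated.
- *That prior stroke cannot be dealt with at all.* A covariate term fails, but restriction to first-ever strokes works.
- *That confounding by treated hypertension, moyamoya disease or AVM is substantial.* Hypertension history is matched, and Table 2 names the other two only as stroke etiologies.
- *That Aim 2 is compromised.* Recurrence is a follow-up outcome after the index stroke. Controls' earlier strokes do not enter that rate in ASPP women.

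**Conclusion.** The defect is real and confined to one comparison. As written, controls for the Aim 1 risk-factor analysis are barred for any earlier stroke and cases are not. Any prior-stroke odds ratio from that comparison is invalid as soon as one case has such a history, whatever the truth. This part needs no prevalence assumption beyond there being at least one such case.

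Bias in closely tied factors runs in the same direction. Its size depends on a prevalence that the article does not give, and it is probably small: at most 4 of 400 controls are displaced at an assumed 1%. The nonpregnant-stroke comparison, the within-case prognosis analyses and Aim 2 are not affected in this way.

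The conclusion assumes that the stated case definition is complete. If the authors meant first-ever stroke in cases, or no stroke in the index pregnancy for controls, the wording should say so.

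**What to change.** Restrict the Aim 1 comparison with pregnant/puerperal controls to ASPP cases with first-ever stroke, and do not report prior stroke or prior cerebrovascular disease as a risk factor from it. Stroke history is already mandatory in Table 1, so no new data are needed. The cost is that cases with prior stroke and their matched controls leave this one analysis (2 pairs of 400 at an assumed 0.5% among cases, 6 at 1.5%), and its findings then apply to first-ever ASPP. All cases stay in the other analyses.

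Alternatively, if controls can still be selected, define them as women with no stroke in the index pregnancy or puerperium, whatever their earlier history, and keep prior stroke as a covariate. This makes prior stroke estimable, but it changes the control group described in the Abstract for the whole study. It is therefore more than a change of wording, and it may come too late, since the inclusion period ended in November 2024.
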